## Discussion

This trial will examine whether BFR resistance exercise with very low load and low volume will present effects similar to those of the HIRE on pain, muscular performance, physical function, disease severity, and quality of life in patients with knee OA. Although previous studies have shown positive effects of BRF exercises, the true efficacy of this intervention is hampered by the matching of the total exercise volume compared with HIRE [14]. In addition, no study has evaluated the effects of BFR exercise with very low load (10% of 1-RM) and low volume in patients with knee OA. If effective, BFR exercise with 10% of 1-RM can be an interesting treatment for generating lower joint overload and consequently lesser pain during exercise.

The present study can be considered of high methodological quality because it is randomized and prospectively registered, masks the evaluators and patients, concealed allocation, and used an intention-to-treat approach. Sample size was calculated to provide adequate statistical power to identify possible differences in the study primary outcome. In addition, the 3-month follow-up will enable verification of the persistent effects of BFR exercise in patients with knee OA, thus filling this gap since studies on this topic generally assess the effects only immediately after treatment.

The exercise load will be periodically adjusted, thus maintaining the overload principle of strength training. We will estimate the 1-RM from a submaximal test (7–10 RM test) to minimize the pain interference in the load determination. In addition, to avoid a possible measurement bias (gain strength due to learning with the test and not due to neuromuscular adaptations) we choose to measure the strength in three different ways (isometric, isokinetic and 7-10 RM test). [46]. Another strength of this trial is external validity. In order to enable extrapolation of the study findings to a larger portion of the population, it was decided not to limit the participation of patients according to gender, unilateral or bilateral involvement, and the use (or not) of medications. The randomization will be balanced and the statistical analysis will be adjusted according to these factors to minimize possible confounding factors due to this greater sample coverage.

This protocol is not free of limitations. First, the percentage of occluded blood flow will not be measured; instead, the percentage relative to the TRP will be calculated; therefore, it is not possible to guarantee the exact amount of BFR. Furthermore, the TRP will be measured at rest, and therefore it will not be possible to guarantee that the amount of restricted blood flow will be the same during exercise since the muscle hemodynamics may be altered because of the action of the muscular pump and release of vasoactive substances. Another limitation of the study is the impossibility of masking the therapist. In conclusion, the results of this trial may indicate the very-low load and low-volume BRF exercise as an effective treatment for knee OA, generating lower joint pain during exercise and increasing adherence and satisfaction with the treatment.

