**Discussion:**

If the improvements in the outcomes are similar in the two groups, BFR exercise with reduced load and volume may be an interesting alternative in the treatment of knee OA, especially when exercises with high loads generate joint pain.

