## Background

Osteoarthritis (OA) is the most common type of arthritis and is characterized by inflammation and major structural changes in the joint [1, 2]. This condition is debilitating because of pain and physical disability, leading to a significant reduction in quality of life [3]. The knee joint is strongly affected by OA, and the weakness of the quadriceps muscle is a major risk factor for knee OA [4].

Strengthening knee extensor muscles is recommended as a key point in reducing pain and disability in these patients [5], and resistance exercises with loads greater than 60% of 1 maximal repetition (1-RM) are classically prescribed to gain strength [6, 7]. However, movements with high loads in the knee with OA can aggravate pain, swelling, and inflammation [8] and consequently reduce adherence to exercise [9]. Resistance exercise with blood flow restriction (BFR) has recently been considered in the treatment of knee OA [10, 11]. BFR resistance exercise is usually performed with lower load (20–30% of 1-RM) combined with a pneumatic cuff inflation that reduces arterial flow and limits the venous return, thus elevating metabolic stimulus in working muscles [12].

BFR exercise may be useful in knee OA treatment because of the possibility of strength gains associated with lower levels of pain, perceived exertion, overload, and joint stress during the training sessions compared with high-intensity (≥60% of 1-RM) resistance exercise (HIRE) without BFR [13–16]. However, it is unclear whether BRF is really required, even in resistance exercises with loads less than 30% of 1-RM [8, 17]. In subjects with knee OA, 8 weeks of resistance training with high (60% of 1-RM) or very low (10% of 1-RM) load without BFR induced similar improvement in pain and muscle function, as the total exercise volume (series × repetitions × load) was paired [8]. In addition, regardless of the load (20% or 50% of 1-RM), exercise volume, or BFR, healthy and untrained individuals presented similar strength increases after 8 weeks of resistance training in which the repetitions were performed until failure [17].

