## Methods

### Study design

This is a prospectively registered, two-arm randomized placebo-controlled trial with concealed allocation, blinded measurers and volunteers, intention-to-treat analysis, and 3 months of follow-up (Fig. 1). Subjects with knee OA will be recruited via online media advertisement, personal invitation, telephone, and SMS. Volunteers will be randomly allocated to the BFR exercise group or HIRE group, and the outcome measures will be evaluated in the time points shown in Table 1.

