### Intervention

The intervention will consist of two weekly sessions with about 60 min of duration each during 12 weeks for a total of 24 sessions. The volunteers will be re-evaluated after 12 weeks and from then on will be guided to practice exercises according to their own volition [20]. In both groups, the sessions will be started with 5 min of light-intensity warm-up on a stationary bike. All subjects included will be instructed not to initiate regular exercises beyond treatment sessions [8, 18]. Both groups will perform bilateral strengthening of the thigh muscles through squatting exercises on the hack machine (angle between 0° and 60° of knee flexion) and leg extension exercises (angle between 90° and 45° of knee flexion) [11, 20]. These amplitudes of movement were selected to minimize the load of the patellofemoral joint during the exercises [24].

In addition to exercises to strengthen the thigh muscles, trunk, hip, and calf exercises will be performed for both groups. High- or low-intensity exercises for strengthening thigh muscles are strongly recommended [25]. Although other studies have focused only on strengthening thigh muscles [8, 11, 18, 20], we chose an overall treatment because of the pathophysiology of knee OA [26] and because there is strong evidence that associating knee exercise and training of proximal and distal muscles to this joint is effective in patients with knee pain [27, 28]. The detailed exercise protocol is shown in Table 2.

**Table 2 Tab2:** Treatment protocol performed by the high-intensity resistance exercise group and blood flow restriction exercise group (adapted from Bryk et al. [15], 2016)

High-intensity resistance exercise group	
- Hamstring stretching, three repetitions of 30 s	
- Bridge with isometric contraction of the transversus abdominis, CORE training, three repetitions of 30 s ^+^	
- Hip abduction with weights (lying on side), three sets of 10 repetitions ^+^	
- Calm exercises (lying on side) with elastic band, three sets of 10 repetitions ^+^	
- Calf raises, three sets of 10 repetitions ^+^	
- Sensori-motor training (standing) on a mini-trampoline, three repetitions of 30 s	
- Squats on a hack machine, 0°–60° of knee flexion, three sets of eight repetitions *	
- Seated knee extensions (machine), 90°–45° of knee flexion, three sets of eight repetitions *	
Blood flow restriction exercise group	
- Hamstring stretching, three repetitions of 30 s	

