### Sample size estimates

It is estimated that a sample size of 32 patients per group would be necessary to test our research hypothesis on the primary outcome (knee pain). The parameters utilized to sample size calculation included an intergroup variability (σ) in the VAS gain of 21% for both groups [44]; a non-inferiority limit (d) of 14%, which is less than the minimum clinically perceptible difference, usually considered to be 15% for the VAS [45]; a type-I error of 5% (α =0.05); a power of 80% (β=0.20) and a dropout rate of 15%.

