### Statistical analyses

The data distributions of normality will be evaluated by the Kolmogorov–Smirnov test. In the case of normal distribution, an analysis of covariance (ANCOVA test) with Tukey’s post hoc will be used to test the differences between groups. The between-group mean difference, 95% confidence interval, and effect size (Cohen’s f) will be reported. The Kruskal–Wallis test will be used for non-normal data distribution, and the effect size will be calculated with Cohen’s r. All participants will be included in the analysis following an intention-to-treat approach.

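### A result similar to HIRE cannot show that the BFR regimen is effective: the design is active-controlled with a shared programme, not placebo-controlled

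*Protocol article*

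**What the plan says.** - **Design label.** Study design describes a "two-arm randomized placebo-controlled trial" with two groups, BFR exercise and HIRE.
- **Where the placebo sits.** Under High-intensity resistance exercise, the HIRE group trains at 60% of 1-RM wearing the cuff at 10 mm Hg. The BFR group trains at 10% of 1-RM with the cuff at 60% of total restriction pressure.
- **What is shared.** Under Intervention, "trunk, hip, and calf exercises will be performed for both groups". Table 2 lists the same stretching, core, hip, calf and mini-trampoline items for both arms. Under Masking/blinding, both groups are told that BFR works.
- **Margin.** Sample size estimates gives "a non-inferiority limit (d) of 14" per cent, justified as lying below the minimum perceptible difference of 15%.
- **Analysis.** Under Statistical analyses, ANCOVA "will be used to test the differences between groups", with a 95% confidence interval for the between-group difference.
- **Conclusions anticipated.** The Abstract says: "If the improvements in the outcomes are similar in the two groups, BFR exercise with reduced load and volume may be an interesting alternative". The closing sentence of the Discussion goes further: "the results of this trial may indicate the very-low load and low-volume BRF exercise as an effective treatment for knee OA". The limitations listed just before it concern the measurement of restriction and the unmasked therapist.

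**The concern.** Finding two active arms alike shows that a treatment works only if something establishes that the comparator worked in this setting, and by more than the margin. Here nothing does. The arms differ only in two thigh exercises and the cuff setting, on top of a common programme and a common message. The margin is not tied to what HIRE adds to that programme. The word placebo in the design label invites a reader to think that the cuff's effect is being controlled for, which it is not.

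At stake is what the trial may claim. A similar result could be published as evidence that low-volume BFR exercise is effective for knee OA when the thigh regimens added nothing, or when the cuff was inert. It would also leave open the question raised in the Background, whether gains come from the BFR stimulus or from exercise volume.

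**Working it through.** **1. What the comparison can isolate**

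| Component | BFR arm | HIRE arm |
|---|---|---|
| Stretching, core, hip, calf, sensorimotor | yes | the same |
| Message that BFR works | yes | the same |
| Thigh load | 10% of 1-RM | 60% of 1-RM |
| Volume per thigh exercise (× 1-RM) | 0.1 × 75 = 7.5 | 0.6 × 24 = 14.4 |
| Cuff | 60% of total restriction pressure | 10 mm Hg |

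Load, volume and cuff pressure change together. Isolating the cuff would need 10% of 1-RM with a sham cuff; isolating the thigh regimen would need the shared programme alone. Neither arm exists. The Background itself cites a study in which "high (60% of 1-RM) or very low (10% of 1-RM) load without BFR induced similar improvement in pain and muscle function", with volume paired. Volume is not paired here, so that result does not transfer directly, but it shows that an inert cuff cannot be dismissed.

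**2. The plan's own figure**

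Inputs from Sample size estimates: SD 21, limit 14, α 0.05, power 80%, dropout 15%. Sidedness is not stated; one-sided 5% reproduces the plan.

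n = 2 × [21 × (1.645 + 0.842) / 14]² = 27.8, so 28 evaluable per group. Then 27.82 × 1.15 = 31.99, the stated 32 per group (27.82 / 0.85 = 32.7 gives 33). At one-sided 2.5% the result is 36, or 43 with dropout, which does not match.

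The Abstract and the eligibility section give 40 patients in total, that is 20 per group if allocation is equal. That conflict is a separate matter; both sizes are shown below.

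**3. How often the arms would look alike**

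Let d be the true advantage of HIRE in VAS points, with BFR's thigh regimen adding nothing. The document gives no value for d, so d is an assumption.

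- SE = 21 × √(2/n): 6.64 at n = 20, 7.20 at n = 17 (20 less 15%), 5.61 at n = 28.
- Non-inferiority is shown when the upper confidence bound is below 14. The normal approximation is Φ[(14 − d)/SE − z]. For n = 20, d = 0: 14/6.64 − 1.645 = 0.463, and Φ = 0.678. The noncentral t gives 0.665. The table uses the noncentral t.
- The 95% interval column uses one-sided 2.5%.
- The last column is the chance of two-sided p > 0.05.

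| n per group | d | Non-inferior, one-sided 5% | Non-inferior by 95% CI | Not significant |
|---|---|---|---|---|
| 20 | 0 | 66% | 54% | 95% |
| 20 | 5 | 38% | 26% | 89% |
| 20 | 10 | 15% | 9% | 69% |
| 20 | 14 | 5% | 2.5% | 46% |
| 17 | 0 | 60% | 47% | 95% |
| 28 | 0 | 79% | 69% | 95% |

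A simulation of 200,000 trials agrees at d = 0 (66%, 60% and 79% at one-sided 5%).

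**4. Reading**

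The d = 0 rows cover two situations: neither thigh regimen adds anything, or the cuff is inert and very-low-load exercise alone equals HIRE. In both, the chance of a similar result is simply the trial's power at zero difference. It would be the same if both thigh regimens truly worked equally well, which is why the result cannot tell these cases apart.

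**The case against.** The strongest reply is that the document contains no rule turning similarity into effectiveness. The Abstract promises only an interesting alternative, one sentence of the Discussion makes effectiveness a condition, and the closing sentence is hedged and also anticipates less pain during exercise and better adherence and satisfaction, which are between-arm differences. This stands: a reader might infer that effectiveness is to be declared from similarity alone, and the text does not go that far. But those further outcomes are secondary and do not establish an effect on knee pain after 12 weeks.

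A reader might also infer that BFR would be called similar most of the time even if it adds nothing. The table does not support that in general: when HIRE adds 10 to 14 points, a non-inferiority test finds similarity in only 15% to 5% of trials. It holds when d is near 0, or if a non-significant difference were read as similarity, a rule that the document does not state.

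Nor does the document say that the shared exercises alone are effective. The evidence cited under Intervention is that "associating knee exercise and training of proximal and distal muscles to this joint is effective in patients with knee pain", a combination that includes knee exercise. The same section strongly recommends thigh strengthening, so HIRE is a reasonable active comparator. That does not quantify what it adds to this programme.

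Finally, comparing two regimens is a legitimate aim, and further arms are a design choice. That is accepted. The point concerns the claim and the label.

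**Conclusion.** The point holds as one about what the trial may claim. The design supports *not worse than HIRE in knee pain by more than the stated limit, when both are given with the same programme*. It does not support effectiveness of the BFR thigh regimen or of the cuff, and it is not placebo-controlled in the sense that the label suggests.

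Size: if neither thigh regimen adds anything, a favourable result at 20 per group is expected in about 66% of trials at one-sided 5%, about 54% by the reported 95% interval, and 95% if it means non-significance. The non-inferiority test is protective once HIRE has a real advantage near the limit. These figures rest on the plan's SD of 21 and limit of 14, equal groups, t tests without covariate adjustment, and assumed values of d.

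**What to change.** **(a) Conclusion.** In the Abstract's Discussion and in the opening and closing text of the main Discussion, state that a positive result means that BFR exercise at 10% of 1-RM is not worse than HIRE in knee pain by more than the stated limit when both are given with the same programme. Drop the description of BFR exercise as an effective treatment. Add to the limitations that the design cannot separate the cuff's effect from that of very-low-load exercise or from the shared programme.

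**(b) Label.** In Study design, replace the placebo-controlled label with *active-controlled, with a sham cuff in the HIRE group*.

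The VAS change within each arm, with its 95% confidence interval, may be reported descriptively. It should not become a gate or be offered as proof of effectiveness. Within-arm change includes natural course, regression to the mean and the shared programme, so a gate would pass when that programme did all the work. In simulation with 20 per group, also requiring the HIRE arm's interval to exclude no improvement would cut a non-inferior result from 66% to about 25% if both arms truly improved by an assumed 10 mm.

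The cost is a few sentences and a more modest claim. No patients, arms or visits are added.

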## Trial status

At the time of manuscript submission, the volunteers were being recruited.

## Abbreviations

1-RM: 1 maximal repetition
BFR: Blood flow restriction
GPE: Global perceived effect
HIRE: High-intensity resistance exercise
OA: Osteoarthritis
RTD: Rate of torque development
TRP: Total restriction pressure
VAS: Visual analog scale
